**3.12.3 Anthropometry Measurements**

Section nine is the anthropometric measurements that consist of weight and height. Height will be measured using a SECA Body Meter Model 208 (Rampal, Rampal, Azhar, & Rahman, 2008; Rampal et al., 2009) to the nearest 0.1cm. The respondent will be asked to stand and look straight, barefooted with heels resting together. Height measurement which appears in the read-off area will be recorded. Weight of student will be measured using digital bathroom scale, TANITA Model HD 309 (Rampal et al., 2008; Rampal et al., 2009) to the nearest 0.1kg. The student will be requested to remove slippers or shoe and anything in the pocket. He/she will then be asked to stand upright on the scale and the measurement will be taken. Height and weight measurements will be used to assess students’ body mass index (BMI) as a proxy to their nutritional status in terms of underweight, normal, overweight, and obesity. Height and weight will be measured by qualified health staff. Measuring instruments will be standardized on a daily basis before they are used.

**3.12.4 Blood Pressure Measurements**

Section ten is the blood pressure measurements. Two blood pressure readings will be taken with an Omron HBP-1100 automated BP monitor. This will be measured by qualified health staff with the student comfortably seated for five minutes with the legs not crossed and the back and the arm supported before measurements will be taken. A minute’s rest interval will be allowed after the first reading before the second measurement will be taken (Pickering et al., 2005). The average of the two will be used to classify students.

**3.13 Quality Control of Study Instruments**

**3.13.1 Validity of Questionnaire**

Generally, the validity of an instrument refers to how accurately the instrument measures what it is actually intended to measure. The study instruments in this research will be face validity and content validity.

**3.13.2 Face Validity**

Face validity establishes whether the measure under study seems to be assessing the intended construct under study. The questionnaire will be face validated among a convenient sample of 50 students. They will be asked to assess each of the questionnaire in order of questions (good, average or poor), clarity (clear, average or confusing) and its appropriateness (good, average or poor).

**3.13.3 Content Validity**

A content validity will be executed to determine the validity of the questionnaire. Content validity involves verifying all questions in order to systematically examine the test content to know if it is representative of the sample to be measured. In other words, it is the content of the instrument measuring the intended variables of the research. The content validity will be determined by the supervisory committee from the Community Health Department, Universiti Putra, Malaysia, who will check on the content of the questionnaire. They will then make suggestions to improve these measures. They will check the extent to which the items will be representative concept being measured. The content validity of questionnaire will then be evaluated by specialist in the field of epidemiology, cardiology, and community health.

**3.13.4 Validity of the Anthropometric Measurement**

Anthropometric measurements in this study are weight, height, and blood pressure. All students in the study will be measured equally with the same weight, height, and blood pressure instruments. The study protocol procedures (including measurements of weight, height and blood pressure) will be reviewed with the study team through training sessions before the study will commence. The study instruments will be calibrated daily before use.

**3.13.5 Reliability of Questionnaire**

Reliability refers to the extent to which a questionnaire, test or observation or any measurement procedures yields the same result on repeated trials. It can also be said to be the strength, consistency or reproducibility of scores over time. Training sessions by the researcher and the two clinicians will be conducted for qualified health staff who will take anthropometry and blood pressure measurements to reduce inter and intra observer variability in the measurements in order to increase the reliability of instruments and develop the skill of measurements in order to collect accurate data.

**3.14 Implementation of Intervention**

The CVD risk factor reduction intervention module is basically divided into two sections and will be guided by the IMB model. These are the Health Education and the Physical Activity Modules. The interactive health education sections, the researcher will do education in the schools on CVDs, its risk factors, causes, development and prevention among others in the intervention schools. The intervention schools will be visited three times in a week for a period of six months. Each section of the health education will last for about an hour with a break, and would be followed by questions, answers and discussions.

The physical activity module which consist of aerobics and anaerobic exercises will be delivered by a physical education health instructor in Kintampo health research center (Ghana health service). The instructor will teach students first on the various physical activities and then take them to the school field to undertake the activities. Same exercises will be carried out in the intervention schools. Each physical activity session that will be given to respondents in the intervention group will last for about 25-30 minutes. A summary of the intervention is shown in Table 3.4.

**Table 3.4 : Summary of intervention module**

**MODULE COMPONENTS FORM OF**

**ESTIMATED**

**DELIVERY TIME**

ur per

| **Health**  **Education**  **Module** |  | Module introduction |  Lectures   Discussions | One ho  session |
| --- | --- | --- | --- | --- |
|  |  | CVD introduction |  | |
|  |  | CVD risk factor introduction |  |  |
|  |  | Harmful effects of smoking quitting smoking |  |  |
|  |  | Barriers to quitting smoking |  |  |
|  |  | Health benefits of quitting/not initiating smoking |  |  |
|  |  | Physical activity introduction |  |  |
|  |  | Simple physical activities/exercises |  |  |
|  |  | Fruits and vegetables introduction |  |  |
|  |  | Fruits and vegetables intake/selection |  |  |
|  |  | Introduction to the types of fats |  |  |
|  |  | Outcomes of high fat intake on  health |  |  |
|  |  | Harmful effects of obesity |  |  |
|  |  | Harmful effects of excessive sugar intake |  |  |
|  |  | Promotion of frequent water  intake |  |  |
|  |  | Harmful effects of excessive salt intake |  |  |
|  |  | Harmful effects of alcohol |  |  |
|  |  | Quitting alcohol |  |  |
|  |  | Barriers to quitting alcohol |  |  |
|  |  | Health benefits of quitting/not initiating alcohol |  |  |

**Physical**

**Activity Module**

 Aerobics

Anaerobic:

 Lunge with twist

 Jumping jacks

 Abdominal crunch

 Hamstring stretch

 Wall sit

 Side arm and leg raise

 Push ups

 Sit and reach

 Sit ups

 Knee to chest

 Leg raise

 Squat

Hands on (Field exercise)

25-30 minutes per session

**3.15 Variables**

**3.15.1 Independent Variable**

The independent variable of this study is the behavioral modification intervention program to reduce cardiovascular disease risk factors based on the IMB model among secondary school students in two districts of Brong Ahafo, Ghana.

**3.15.2 Dependent Variables**

The dependent variables of this study are sub divided into primary and secondary outcomes. There were;

i. The primary outcomes are CVD knowledge and its risk factors, motivation, behavioral skills, physical activity, smoking, alcohol consumption, and dietary intake.

ii. The secondary outcomes are body weight, BMI, diastolic and systolic blood pressures.

**3.15.3 Confounders**

The confounders in this study are age, gender, ethnicity, monthly pocket money,

family history of obesity, parent’s education and their occupation.

**3.16 Operational Definition of Terms**

**3.16.1 Body Mass Index**

Weight in kilograms (kg) and height in meters (cm) were measured to determine BMI calculated as weight in kilograms divided by the square of height in meters (kg/m2). Subjects will be classified based on mean BMI for age and gender for children and adolescents. Adolescents were categorized into four groups which were underweight, normal weight, overweight, and obese with cut off points of <5th, 5th to < 85th, 85th to < 95th and ≥95th percentiles of the WHO standard respectively (Barlow, 2007; WHO, 2007).

**3.16.2 Hypertension**

Hypertension, also referred to as high or raised blood pressure is defined as a condition in which the blood vessels have persistently raised pressure thereby putting the blood vessels under stress. Diastolic and systolic BP will be measured in millimeter mercury (mmHg). According to the fourth report on the diagnosis, evaluation, and treatment of

high blood pressure in children and adolescents (National Institute of Health, 2005), blood pressure (DBP or SBP) is classified into normal (≥ 60th and < 90th) pre- hypertension (≥ 90th and < 95th), hypertension stage 1 (≥ 95th and < 99th) plus 5 mmHg, and hypertension stage 2 (≥ 99th) plus 5 mmHg.

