Obesity has been a major problem in recent times. Globally, the prevalence of this risk factor has more than doubled since 1980 and 2014. There were 11% males and 15% females aged 18 years and older who were obese globally in 2014 (WHO, 2014). Thus half a billion adults worldwide are obese. Obesity is a major risk factor of diabetes, hypertension, coronary heart disease and stroke. Overweight and obesity are defined as BMI ≥25kg/m2 and ≥30kg/m2 respectively accounted for 3.4 million deaths in 2010 and 93.6 million Disability Adjusted Life Years (DALYs) (Cawley, Meyerhoefer, Biener, Hammer, & Wintfeld, 2015; WHO, 2014). The prevalence of childhood obesity is becoming a major challenge especially in low and middle income countries. This is as a result of overindulgence in consumption of high caloric foods, activities such as watching television, playing video games and the internet and other forms of physical inactivity (WHO, 2014). A nationwide study among secondary school students in Ghana reported that 8% of the students were either overweight or obese (MOH, 2012).

Hypertension is a major CVD risk factor (Chiolero, Bovet, & Paradis, 2013; WHO,

2014). The global prevalence of hypertension which is defined as systolic and/or diastolic blood pressure of ≥140/90 mmHg in adults aged ≥ 18 years was around 22% in 2014. The highest prevalence of hypertension across the WHO regions is in Africa, at 30% with the lowest prevalence in the region of the Americas at 18% (WHO, 2014). An estimate of 9.4 million people died worldwide in 2010 as a result of hypertension. The prevalence of hypertension in Ghana is about 48% as reported by the GHS (2017b) and has consistently ranked among the top ten causes of outpatient morbidity, admission, and death. The research was carried out in Ghana among 201 youth from three communities between the ages of 12-24 years found that 32.3% and 4% were pre-hypertensive and hypertensive respectively (Afrifa-Anane, Agyemang, Codjoe, Ogedegbe, & de-Graft Aikins, 2015).

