**3.17.3 Inferential Statistics**

Chi-square tests will be performed to compare baseline characteristics of groups by their socio-demographic factors, family factors, CVD knowledge, motivation, behavioral skills, physical activity, smoking status, alcohol intake, BMI, systolic and diastolic BP. Independent t-tests will be performed to determine the between groups differences of total knowledge, motivation, behavioral skills, physical activities, dietary intake, BMI, diastolic and systolic BP. At six months post intervention, the independent and paired sample t-tests would be performed to determine the between and within group differences of variables respectively. Chi-square and the McNemar tests will also be performed on smoking status and alcohol intake at six months to determine the difference between and within groups since the variables are categorical variables.

A mixed design repeated measures analysis of variance (ANOVA) will be performed after checking that there is no substantial non-normality of residuals to determine the between and within group differences and its interactions on time differences on CVD knowledge, motivation, behavioral skills, physical activity, dietary intake, body weight, BMI, diastolic and systolic BP. Intention-to- treat (ITT) analysis will be the method that will be used to handle missing data in the analysis. Replacement of data will then be conducted for each missing variable using the multiple imputation method, following which Generalized Linear Mixed Model (GLMM) analysis will be performed to determine the overall effectiveness of the intervention study.

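### The blood pressure classes in Section 3.16.2 start at the 60th percentile, so lower readings have no class, and the 5 mmHg term at the upper end can be read two ways.

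*Protocol*

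**What the plan says.** Section 3.16.2 of the protocol sets four classes by percentile and attributes them to a published report on blood pressure in children and adolescents.

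- Normal: pressure "is classified into normal (≥ 60th and < 90th" percentile).
- Pre-hypertension: from the 90th to below the 95th percentile.
- Stage 1: "hypertension stage 1 (≥ 95th and < 99th) plus 5 mmHg".
- Stage 2: "hypertension stage 2 (≥ 99th) plus 5 mmHg".

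The rule is introduced with the words "blood pressure (DBP or SBP) is classified into normal". It does not say whether each pressure gets its own class or the two are combined.

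The classes are meant to be used. Section 3.12.4 takes two readings and states: "The average of the two will be used to classify students". Section 3.17.3 states: "Chi-square tests will be performed to compare baseline characteristics of groups", and its list of variables includes systolic and diastolic pressure. The same section then lists both pressures again for t-tests.

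The blood pressure hypothesis (Section 1.6, number 9) concerns mean diastolic and systolic pressure. Section 3.15.2 names the two pressures themselves as secondary outcomes.

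**The concern.** A classification rule has to give every possible reading exactly one class. This one has a floor under its lowest class and nothing beneath the floor, so an ordinary reading falls outside the scheme. The neighbouring BMI definition in Section 3.16.1 has no such floor: its lowest class is everything below the 5th percentile, and the four classes meet without gaps.

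At the upper end, the bracket for stage 1 closes before the 5 mmHg is added. Two people applying the text could class the same raised reading differently.

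At stake are the class assigned to each student and any baseline table or chi-square test built on the classes. Staff would have to leave many students out or make up a class for them, and the protocol does not say which.

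**Working it through.** The protocol states no share of students per class, so there is no figure to reproduce. The check asks whether the printed intervals cover the scale and, where they do not, how many readings are affected.

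**Inputs from the protocol**
- Class limits: Section 3.16.2.
- Planned participants: 848 (Section 3.11).
- Survey of Ghanaian youth cited in Section 1.1: 32.3% pre-hypertensive and 4% hypertensive, together 36.3%.

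**Assumptions, not in the protocol**
- Pressures are normally distributed.
- The correlation between systolic and diastolic pressure is between 0 and 1.
- The standard deviation (SD) is 8 to 12 mmHg.

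**Gap below the 60th percentile**

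1. One pressure, students like the reference population. By the definition of a percentile the share is 0.60, and 0.60 × 848 = 509.

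2. The higher of the two pressures sets the class. A student is then unclassified only if both are below the 60th percentile. The share is the bivariate normal probability that both standardised values lie below z(0.60) = 0.253.

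| Assumed correlation | Share unclassified | Of 848 |
|---|---|---|
| 0 | 0.60 × 0.60 = 36% | 305 |
| 0.5 | 44% | 372 |
| 0.7 | 48% | 405 |
| 1 | 60% | 509 |

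3. Pressures higher than the reference. Suppose 36.3% lie at or above the 90th percentile, as the cited survey would imply if it used these cut-offs. The upward shift is z(0.90) − z(0.637) = 1.282 − 0.350 = 0.931 SD. The share below the 60th percentile is Φ(0.253 − 0.931) = Φ(−0.678) = 24.9%, about 211 of 848 per pressure. A milder shift, with 20% at or above the 90th percentile, gives 43%.

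Steps 2 and 3 are alternatives. Stacking them, with both pressures shifted that far, would give between 0.249² = 6% (correlation 0) and 25% (correlation 1). The protocol does not say whether the survey's 36.3% was counted on one pressure or on either, so this combination is only a lower extreme.

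**The 5 mmHg term**

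- Reading A, as punctuated: 5 mmHg is added to both limits. Stage 1 runs from the 95th percentile + 5 to below the 99th + 5. Pre-hypertension ends at the 95th, so readings from the 95th to below the 95th + 5 have no class.
- Reading B: 5 mmHg is added only to the 99th-percentile limit. Stage 1 runs from the 95th to below the 99th + 5, where stage 2 begins. There is no gap.

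The size of the gap under reading A, in a reference population, is Φ(1.645 + 5/SD) − 0.95:

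| Assumed SD (mmHg) | Share of all readings | Share of readings at or above the 95th |
|---|---|---|
| 8 | 3.8% | 77% |
| 10 | 3.4% | 68% |
| 12 | 3.0% | 61% |

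**After correction**

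With an open-ended lowest class and one boundary between each pair of neighbouring classes, the unclassified share is 0%.

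**The case against.** The strongest reply is that little depends on the classes. The blood pressure hypothesis, the secondary outcomes, the t-tests and the mixed-design ANOVA all work with the pressures as continuous measurements. Even the categorical use at baseline is partly inferred, because the chi-square list in Section 3.17.3 also names score variables and does not say how pressure is grouped. The floor also leaves the 90th-percentile line between normal and raised pressure where it was. All of this stands, and it limits the consequence. It does not remove the defect: Section 3.12.4 says students will be classified, and this is the only rule for doing so.

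A statistical analysis plan might settle how the two pressures combine. That is fair, and by itself it would not be a finding. It becomes worth settling because the definition has to be rewritten anyway.

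A reader might infer more than the text supports:

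- That 60% of students are certain to have no class. The figure holds per pressure and only under the reference distribution.
- That a second gap certainly exists above the 95th percentile. It depends on reading A, and reading B is tenable because it matches the stage 2 limit.
- That students aged 18 to 19 fall under two conflicting definitions, since Section 1.1 mentions "systolic and/or diastolic blood pressure of ≥140/90 mmHg in adults aged ≥ 18 years". That sentence explains how a global adult prevalence was defined; it is not a study definition.
- That a reported hypertension proportion will be inflated by a reduced denominator. The protocol sets no such proportion as an outcome and does not say that unclassified students leave the denominator. The survey's 4% also cannot be paired with 60% below the 60th percentile: with 36.3% at or above the 90th, only 3.7% would remain in between.
- That a safety review would miss raised readings. The protocol describes no safety review that uses these classes.

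**Conclusion.** The point holds in limited form. The absence of any class below the 60th percentile is certain from the text. Its size is not fixed by the protocol: 60% of readings per pressure under the reference distribution, 36% to 60% of students if the higher pressure decides, and about 25% per pressure if this population runs as high as the cited survey suggests. The 5 mmHg wording is an ambiguity. Under one of its two readings it leaves about 3.0% to 3.8% of a reference population unclassified.

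The consequence is confined to the classification of students and to categorical blood pressure results at baseline. The analyses of mean systolic and diastolic pressure are unaffected. The definition should be corrected because it cannot be applied as printed.

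**What to change.** Restate the classes in Section 3.16.2 and reconcile them with the report already cited there, so that every reading falls in exactly one class:

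- Give the lowest class no lower bound, as the BMI classes in Section 3.16.1 already do.
- Write one unambiguous boundary between pre-hypertension and stage 1 and one between stage 1 and stage 2, making clear which percentile limit the 5 mmHg belongs to.
- Say whether systolic and diastolic pressure are classed separately or combined, and if combined, by what rule.

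The cost is the rewording of one definition. The measurements, the sample size and the analyses of mean pressure do not change.

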**3.16.3 Physical Activity**

Physical activity refers to the total number of questions in the PA that were answered by participants.

**3.16.4 Smoking**

Smoking will be categorized into ex-smokers, current smokers, and never smoker. Ever smokers were students who had ever tried smoking before but had stopped. Current smokers are those who are currently smoking tobacco. Never-smokers referred to as students who has never smoked tobacco.

**3.16.5 Alcohol**

This refers to the consumption of alcoholic beverages. These include but not limited to drinks such as beers, wine, ‘’pito’’ (made from fermented cereal such as millet), spirits, and ‘’akpeteshie’’ (made from distilling sugar cane).

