**1.6 Research Hypotheses**

The research hypotheses of this study are:

1. There will be no difference in the socio-demographic characteristics between the intervention and control groups at baseline.

2. The behavioral modification intervention program will be effective in improving the knowledge of CVD and its risk factors, motivation, and behavioral skill score among the participants in the intervention group as compared to control group and also within the groups from baseline to six months among secondary school students in Brong Ahafo, Ghana.

3. The behavioral modification intervention program will be effective in promoting physical activity levels of participants in the intervention group as compared to control group and also within the groups from baseline to six months among secondary school students in Brong Ahafo, Ghana.

4. The behavioral modification intervention program will be effective in reducing the prevalence of smoking among participants in the intervention group as compared to control group and also within the groups from baseline to six months among secondary school students in Brong Ahafo, Ghana.

5. The behavioral modification intervention program will be effective in reducing the prevalence of alcohol consumption of participants in the intervention group as compared to control group and also within the groups from baseline to six months among secondary school students in Brong Ahafo, Ghana.

6. The behavioral modification intervention program will be effective in promoting fruits and vegetable intake among participants in the intervention group as compared to control group and also within the groups from baseline to six months among secondary school students in Brong Ahafo, Ghana.

7. The behavioral modification intervention program will be effective in increasing seafood and water intake and reducing carbohydrates, fats and oils, fried eggs, fried chicken, carbonated drinks, plain sugar, sweet snack, and salted fish intake among participants in the intervention group compared to control group and also within the groups from baseline to six months among secondary school students in Brong Ahafo, Ghana.

8. The behavioral modification intervention program will be effective in reducing body weight and BMI of participants in the intervention group as compared to control group and also within the groups from baseline to six months among secondary school students in Brong Ahafo, Ghana.

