**3.12.2 Questionnaire**

The questionnaire will be pre-tested and assisted self-administered questionnaire in English language as in Appendix. The questionnaire will be divided into ten sections namely, socio demography, dietary intake, smoking, alcohol consumption, physical activity, CVD knowledge, motivation, behavioral skills, BMI (weight and height), and blood pressure (diastolic and systolic). The questionnaires will be administered in a classroom setting in all the selected schools.

Section one of the questionnaire will be used to access students’ age, gender, grade, ethnicity, monthly pocket money, and family history. Data on age will be collected in the form of open ended question and students will fill in the blank space provided. The rest (ethnicity, gender, religion, and family history) are in the form of closed ended questions and students are to choose the answers that will pertained to them.

Section two is a seven-day dietary recall instrument which are foods items mostly consumed in Ghana, the Ghana Demographic and Health Survey, (GDHS), (GSS, 2009; Nti, 2008) to assess dietary consumption. Amounts of each food intake will be stated with the use of handy measure tables (food weights). This are based on the weights of foods with their equivalent handy measure tables which are commonly used

in Ghana (Owusu, Ankrah, Boateng, & Anteh, 1995). Then frequency of consumption of certain foods will be scored based on one (1) for never dietary consumption, two (2) for 2-3 times per week, three (3) for 4-5 times per week, four (4) for 6 times per week, and five (5) for daily intake of a particular food item.

Section three and four are the modified smoking and alcohol questionnaires, Global Youth Tobacco Survey (GYTS) developed by WHO and Centre for Disease Control and Prevention (CDC) (CDC, 2008). It is a school-based adolescents’ self- administered questionnaire which comprised of a set of core questions that will be used to evaluate tobacco and alcohol control and prevention programmes among secondary school students. Students would be classified as never, ever, and current smokers and alcohol consumption. Strict confidentiality will be ensured among researchers to avoid disclosure of smoking and alcohol statuses to school authorities, teachers, or parents.

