**48. Have you ever taken alcohol before?**

1. Yes 2. No **EVERALCO**

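### The primary alcohol outcome is not tied to a category, item or time window, and the tests named for it do not fit the three-level grouping that the protocol states

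*Protocol*

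**What the plan says.** Section 3.15.2 of the protocol makes alcohol a primary outcome: "The primary outcomes are CVD knowledge and its risk factors, motivation, behavioral skills, physical activity, smoking, alcohol consumption, and dietary intake". Hypothesis 5 in section 1.6 expects the programme to be "effective in reducing the prevalence of alcohol consumption of participants in the intervention group as compared to control group", and also expects a change within groups from baseline to six months.

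The operational definition in 3.16.5 reads "This refers to the consumption of alcoholic beverages" and then names kinds of drink. It gives no category, threshold, unit or period. The only grouping is in 3.12.2: "Students would be classified as never, ever, and current smokers and alcohol consumption". Section 3.16.4 explains the categories for smoking ("Ever smokers were students who had ever tried smoking before but had stopped"), but there is no matching text for alcohol.

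The questionnaire in Appendix A offers three measures:
- item 48, "Have you ever taken alcohol before", answered yes or no;
- item 49, whether the student still drinks, answered yes, no or not applicable, with no recall window;
- item 50, number and frequency by type of drink.

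Section 3.17.3 plans the analysis: "Chi-square and the McNemar tests will also be performed on smoking status and alcohol intake at six months", for differences between and within groups. It then plans multiple imputation and a GLMM for overall effectiveness. The mixed-design ANOVA in the same section does not list alcohol.

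**The concern.** The protocol states a hypothesis, a grouping and two tests for this outcome, and they do not fit together.

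- **Prevalence is undefined.** It could mean lifetime use (item 48), current use (item 49) or some frequency cut of item 50. These can give different answers to the same question.
- **McNemar's test takes a paired two-level variable.** The stated grouping has three levels, and no rule collapses them. The usual extension to more levels tests symmetry and has no direction.
- **A three-level chi-square at six months is not a test of a fall.** It responds to any difference between arms, including one in the never/ever split that existed before the programme began. With two schools per arm, randomisation gives little protection against such a difference, and the test uses no baseline value.
- **The ever category is ambiguous.** If it follows the smoking text, it holds both students who quit, which is a success, and students who started and stopped during the trial, which is a failure.

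At stake is a primary outcome whose endpoint could be chosen after the data are seen, and a significant result that need not reflect any change in drinking.

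**Working it through.** The protocol gives no rate, effect size or power for alcohol, so there is no stated figure to reproduce. The check asks what the three-level chi-square responds to.

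**Inputs.** 424 students per arm (3.11) and a significance level of 0.05 (3.17). As assumptions, lifetime use is 42.3% and current use 12.6% in the reference arm. These values appear in the protocol's background (1.1 and 2.6.3.2) but come from two different surveys, and the first is not labelled as lifetime use. They serve only as working values, and other values are shown in step 2. Clustering is ignored, so none of these results is the trial's real power.

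**Formula.** For category proportions c and t in the two arms with mean m, the noncentrality is λ = n × Σ[(c − m)²/m + (t − m)²/m] = 2n × Σ[(c − m)²/m]. Power is the chance that a noncentral chi-square with 2 degrees of freedom exceeds 5.99 (1 degree of freedom for two-level versions).

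**Step 1: can the grouping register quitting?** Never/ever/current is 57.7/29.7/12.6 in one arm and, with half the current drinkers stopping, 57.7/36.0/6.3 in the other.
λ = 848 × 0.0315² × (1/0.3285 + 1/0.0945) = 11.47, so power is 0.87.

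Other assumed levels of current use, with lifetime use held at 42.3%:

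| Current use, control | Relative cut | Three-level | Current yes/no | Lifetime yes/no |
|---|---|---|---|---|
| 12.6% | 50% | 0.87 | 0.88 | 0.05 |
| 12.6% | 30% | 0.40 | 0.43 | 0.05 |
| 25% | 50% | 1.00 | 0.997 | 0.05 |
| 25% | 30% | 0.86 | 0.76 | 0.05 |
| 40% | 30% | 1.00 | 0.96 | 0.05 |

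So the grouping does register quitting. If prevalence is read as lifetime use, quitting leaves it untouched and power equals the significance level.

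**Step 2: does it also respond when current drinking is the same?** Keep current use at 12.6% in both arms and let lifetime use differ.
- 42.3% against 47.3%: λ = 848 × 0.025² × (1/0.552 + 1/0.322) = 2.61, so it rejects 28% of the time.
- 42.3% against 52.3%: λ = 848 × 0.05² × (1/0.527 + 1/0.347) = 10.13, so it rejects 82% of the time.

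The same formula for other assumed pairs, with lifetime use higher in the second arm:

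| Lifetime use, first arm | Current use, both arms | 5 points higher | 10 points higher |
|---|---|---|---|
| 50% | 5% | λ 2.23, 25% | λ 8.95, 77% |
| 42.3% | 12.6% | λ 2.61, 28% | λ 10.13, 82% |
| 30% | 20% | λ 5.03, 51% | λ 17.40, 97% |

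A two-level test of current drinking would reject 5% of the time in every row.

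**Step 3: McNemar's test.** On current against not current it works as intended. As an example, 27 students who quit and 10 who start give an exact p of 0.008. The test is sound once the variable is two-level; the protocol does not say which two levels.

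**The case against.** The strongest reply is that alcohol is measured and the hypothesis can be tested. Section 3.12.2 supplies a grouping, items 48 to 50 collect the data, and the current category can fall. A reader might infer from 3.16.5 alone that the outcome has no measurable definition, or that never/ever/current can never show the hypothesised fall. Neither follows. Step 1 shows the grouping registering quitting, and a zero effect arises only if lifetime use is taken as the endpoint, which the protocol neither adopts nor rules out.

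Further replies have weight:
- A two-by-two chi-square is also two-sided, and its direction is read from the percentages. With two levels, however, the sign of the difference is unambiguous; with three it is not.
- Items 48 and 49 are essentially yes/no, and a prevalence is naturally binary, so McNemar's test may have been meant for one of them. The text does not say which.
- A GLMM is planned, and the abstract gives it group, time and interaction terms. That would address baseline differences, but 3.17.3 does not name the alcohol variable that it models.
- How levels are collapsed is often left to an analysis plan. Here the protocol itself fixes a three-level grouping and a two-level test, so the mismatch is on its own page.

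The reply removes the claim that hypothesis 5 cannot be tested. It does not supply the endpoint.

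**Conclusion.** The point holds in a limited form. A primary outcome lacks a fixed endpoint: no section says which category, item or time window is the prevalence in hypothesis 5. The stated grouping does not suit McNemar's test without a collapsing rule, and the unadjusted six-month chi-square on three levels does not isolate a fall in drinking.

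Under the working values, a prior difference of 5 or 10 points in lifetime use would make that chi-square significant about 28% or 82% of the time with identical current drinking. The other assumed pairs shown give 25% to 51% and 77% to 97%. These figures rest on assumed prevalences and independent students. The direction of the argument does not depend on them, because lifetime use cannot truly fall within a student over six months.

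The documents do not support the stronger conclusion that the hypothesis is untestable. Once current drinking is named, the planned items and models can test it.

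**What to change.** In 3.16.5, define the primary alcohol outcome as current drinking at six months, yes or no, from item 49 with a stated recall window. Smoking items 33 and 34 already use 30 days, which is one option. State that never-drinkers who circle not applicable count as no. Otherwise the imputation in 3.17.3 could treat them as missing and assign them a drinking status.

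In 3.17.3, analyse this variable in the planned GLMM with a logit link, baseline drinking status and school. Use McNemar's test only on this two-level variable. Report lifetime use, the three-level table and item 50 frequency descriptively.

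The cost is small: wording in two sections and one reworded item, used identically at both waves. The three-level test is given up. It can have more power when current use is high (0.86 against 0.76 at 25% current use and a 30% cut) and has slightly less at 12.6%. With four schools the school effect will be estimated imprecisely, and this change does not cure that.
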